#### Imaging and pathology surveillance

At two years following treatment, when feasible subjects will undergo a surveillance 3T MRI using multiparametric sequencing, followed by a combination MRI-guided biopsy and systematic whole gland biopsy (where feasible) for identification of any residual viable tumor. MRI findings and pathology will be compared between groups. If a patient is found to have a biopsy positive for residual adenocarcinoma, additional follow up and possible treatment will be discussed per physician assessment and patient preference.

**Table 4 Tab4:** Schedule of patient assessments through the study period

Schedule of Assessments							Notes
Visit Name	SCR	Simulation & treatment	2-week toxicity assessment^a^	1st year follow up^b^	Follow up years 2-5^c^	Follow up year 6 and thereafter^d^	
Medical history	X						
Concomitant medication review	X						
Adverse events assessment			X	X	X	X	
Physical examination	X			X	X	X	
PSA	X			X	X	X	Staging PSA will be obtained within 1 month prior to enrollment
IPSS	X			X	X	X	
EPIC	X			X	X	X	
SHIM	X			X	X	X	
Hydrogel spacer insertion	X						
Staging PET CT/CT/Bone scan	X						optional
Prostate MRI	X				X		2-year MRI per physician recommendation
Prostate biopsy					X		Following the 2-year MRI– biopsy should be both targeted and systematic

a. For the first three patients. b. During the 1st -year, follow up will be performed at 1, 3, 6, 9, and 12 months. c. Every 6 months. d. Annually

#### Discontinuation/withdrawal

Subjects may voluntarily discontinue participation at any time. If a subject discontinues participation from the study, any remaining clinical and laboratory evaluations that would have been performed at what would have been the next scheduled follow up, such as PSA and quality of life questionnaires, will be obtained at that time. Any patient who may suffer an adverse event will remain in close medical follow up as long as deemed appropriate.

### Statistics and sample size calculation

#### Randomization

The study will utilize a 1:1 randomization between Arm 1: Arm 2, based on the stratification factors described in the Methods section. Randomization will take place in permuted blocks, details of block size known exclusively by the study statistician. The randomization sequence will be uploaded into a restricted-access database (REDCap), details of which known only to the statistician. The database is housed on secure hospital servers at Davidoff Cancer Center. Once a patient is enrolled, the database will be accessed by the primary trial coordinator to obtain the appropriate intervention in sequence, which will then be assigned to the patient.

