### Study design

This is a prospective randomized phase II/III non-inferiority control trial with pre-planned interim analyses for safety signals in the 2-fraction arm. Participating centers will be tertiary, academic hospitals in Israel (updated list available at health.gov.il) with the potential of opening additional sites (limited to the United States and Canada) over the trial period. All aspects of the trial have been approved by the relevant institutional internal review boards. Subjects will be randomized between the standard arm of prostate SABR to 40 Gy in 5 fractions and the experimental regimen of 27 Gy in 2 fractions (Fig. 1). A focal simultaneous integrated boost (SIB) to the MRI-defined dominant intraprostatic lesion (DIL) will be permitted. All patients will undergo trans-rectal ultrasound-guided placement of a radiopaque hydrogel spacer and three gold fiducial intraprostatic markers prior to simulation. Both simulation CT and a planning MRI will be used for target and normal structure delineation, though SABR delivery will not require an MRI-guided linear accelerator (LINAC).

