**Fig. 1 Fig1:**
[figure not shown]
Schema of the SABR-Dual clinical trial

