#### Analysis plan

The primary endpoint of this study is failure from disease progression (FFDP), defined as clinical or biochemical disease recurrence (biochemical failure as per PSA nadir + 2 ng/mL), excluding death. Death with no evidence of progression will be treated as a competing risk in the survival models. This study will utilize both an intent-to-treat and per-protocol analysis of the primary and secondary endpoints, with time-to event duration originating at random assignment. Prognostic characteristics, treatment delivery, and toxicity will be reported using descriptive statistics. Time-to-event endpoints will be calculated using the Kaplan-Meier method [24] and compared using the log-rank test. HRs with 95% CI will be computed using the Cox proportional hazards regression model for the end point–specific hazard. Frequency distributions of grade (0 to 5) for selected adverse events will be compared using x^2^ tests. 2 × 2 sub-tables will be formed to evaluate the differences in risk of grade 2 or 3 events, and relative risk (RR) estimates with 95% CIs will be computed. The definitive analysis is planned to occur at 5 years, with two planned interim safety analysis at mean follow up of one and two years.

Secondary endpoints (unpowered) will include progression free survival (PFS), distant metastasis-free survival (DMFS), prostate cancer-specific survival (PCSS), longitudinal PSA response, and time to salvage treatment, also assessed at five years. Both patient-reported and physician-reported treatment related adverse effects at six months, one, and two years will be compared and reported. In the setting of multiple secondary endpoints, the Benjamini-Hochberg FDR correction procedure will be applied. Treatment related AE will be primarily objectively measured using the EPIC-26 evaluation. MIDs for each of the domains will be set as follows: 5 for bowel and hormonal, 6 for urinary obstructive, 11 for sexual, and 8 for urinary incontinence [25].

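### Randomisation is stratified, but the primary analysis as written uses no strata; analysing by the randomisation factors would give a small gain in precision at almost no cost

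*Protocol article*

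**What the plan says.** The Randomization section of the protocol article states that allocation is 1:1 and "based on the stratification factors described in the Methods section". It adds: "Randomization will take place in permuted blocks, details of block size known exclusively by the study statistician". The sequence is held in a restricted-access REDCap database whose details only the statistician knows.

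The visible Methods text names no stratification factor. The Study design section describes the two arms and refers to Fig. 1, captioned "Schema of the SABR-Dual clinical trial", which is not reproduced in the text available for this review.

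The Analysis plan is fairly specific about the primary comparison. It gives the analysis sets, the time origin and the handling of death without progression, and then says: "Time-to-event endpoints will be calculated using the Kaplan-Meier method [24] and compared using the log-rank test". For the effect estimate it says: "HRs with 95% CI will be computed using the Cox proportional hazards regression model for the end point–specific hazard". Neither sentence mentions strata or covariates.

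The Sample size section sets 228 per arm, a 5-year control rate of 90–91%, 80% power, an α of 0.05 and a non-inferiority margin of 7 percentage points at 5 years.

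**The concern.** Stratified allocation makes the arms more alike on the chosen factors than simple randomisation would. If the factors predict failure, the true sampling variance of the treatment difference falls. An analysis that ignores the strata still estimates the larger variance of an unstratified design, so its interval is wider than the design warrants.

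In a non-inferiority trial the result depends on where the confidence limit falls relative to the margin, so an interval that is too wide costs power. It also helps to fix the choice between stratified and unstratified results before the data are seen. What is at stake here is small, as the working shows.

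**Working it through.** **Inputs from the protocol article (Sample size).** 228 per arm; 5-year control rate 90%, the lower end of the stated 90–91%; margin 0.07; power 80%; α 0.05 with sidedness not stated. Both one-sided 0.05 (z = 1.645) and the lower limit of a 95% interval (z = 1.96) are shown.

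**Reproducing the plan's figure.** For a difference of two proportions with unpooled variance and equal true rates:

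n per arm = (1.645 + 0.842)² × 2 × 0.90 × 0.10 / 0.07² ≈ 227.1, rounded up to 228, which gives 456 in total.

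This matches the stated 456. The plan's calculation is therefore consistent with an unstratified two-proportion method at one-sided 0.05, and it does not depend on any strata.

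**Assumption.** The document gives no strata, no number of strata and no prognostic effect. For illustration, take two strata of equal size with 5-year failure of 5% and 15% (mean 10%).

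**Variance.**
- Ignoring strata: 0.10 × 0.90 = 0.0900.
- Within strata: (0.05 × 0.95 + 0.15 × 0.85) / 2 = 0.0875.
- Reduction: 0.0025 / 0.0900 = 2.8%.

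**Standard error and interval half-width.**
- Ignoring strata: √(2 × 0.0900 / 228) = 0.02810; half-width 4.62 points (z = 1.645) or 5.51 points (z = 1.96).
- Within strata: √(2 × 0.0875 / 228) = 0.02770; half-width 4.56 or 5.43 points.

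**Power, Φ(0.07 / SE − z).**

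| | z = 1.645 | z = 1.96 |
|---|---|---|
| Variance ignoring strata | 80.1% | 70.2% |
| Within-stratum variance | 81.1% | 71.5% |

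The first row treats the estimate as if it really had the larger variance. After stratified allocation it does not; only the estimated standard error is too large. Power of the unstratified test is then Φ((0.07 − z × 0.02810) / 0.02770), which is 80.5% or 70.5%. The gain from changing the analysis alone is therefore about 0.6 points (81.1 − 80.5) or 1.0 point (71.5 − 70.5).

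**Range.** With equal strata, the variance falls by the square of half the gap between the two failure rates.
- Failure 10% and 10%: no reduction, no gain.
- Failure 7% and 13%: 0.03² = 0.0009, a 1.0% reduction; within-stratum power 80.5% against 80.1% at z = 1.645.
- Failure 5% and 15%: as above.

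**Simulation check.** Two equal strata, 228 per arm, one-sided 0.05, 40,000 replicates, with control 5-year rates by stratum running from 90.5%/90.5% to 97%/84%. Unstratified type I error was 0.049–0.052 and stratified 0.052–0.053. Power was 0.817–0.827 unstratified and 0.818–0.836 stratified. The largest gain was 0.836 − 0.827, about 1 point. The Monte Carlo standard error of a type I error near 0.05 is √(0.05 × 0.95 / 40,000) ≈ 0.001. The stratified test is therefore marginally above nominal here, and the unstratified test shows no material inflation.

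**Expected events.** 10% of 456 is 45.6, so about 46 failures. Many small strata would leave some with few or no events.

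**The case against.** The strongest objection is that the Analysis plan never says the comparison is unstratified. A stratified log-rank test and a stratified Cox model would both fit its wording, and such detail is commonly left to a full protocol or SAP, neither of which is shown. This stands to the extent that no explicit rejection of stratification can be claimed. The section is nevertheless detailed about the primary analysis, and the plain reading of an unqualified log-rank test is the ordinary one.

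A reader might infer more than the document supports, in three ways:
- **That the strata cannot be carried into the analysis.** The statistician holds the randomisation sequence in REDCap, so any strata used for allocation can be recovered.
- **That the reference to factors in the Methods leads nowhere.** The visible text names none, but Fig. 1 belongs to the Methods and is not shown. A trial schema may list them, so a failed cross-reference is not established.
- **That non-inferiority could be declared falsely.** Ignoring prognostic strata after balanced allocation errs in the conservative direction, and the simulation shows no material inflation.

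It is also fair to object that the illustrative strata are assumed, that eligibility is already limited to low- and favorable intermediate-risk disease, and that the calculation concerns a difference in proportions, not the hazard ratio. All three points stand. They limit the size of the concern but do not remove it. No narrowing of the hazard ratio interval is claimed.

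**Conclusion.** The point holds as a minor improvement to the analysis. Taken as written, the primary comparison leaves out the factors used to balance the arms, so its interval is slightly too wide when those factors are prognostic. The size is about 1 point of power at most in the cases examined, and close to none if the factors carry little prognostic information. The sample size of 456 is unaffected.

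This rests on reading the unqualified log-rank test and Cox model as unstratified, on assumed equal strata with 5% and 15% failure, and on a 5-year difference in proportions, the scale on which the margin is set.

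**What to change.** In the Analysis plan:
- Stratify the log-rank test and the Cox model by the randomisation factors.
- Use a stratum-weighted difference in 5-year freedom from disease progression for the comparison with the 7-point margin.
- Fix in advance a rule for pooling sparse strata, given about 46 expected failures.

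As an editorial matter, name the factors in the Randomization section, or point to Fig. 1 if they are listed there.

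The cost is a few sentences plus one real decision, the pooling rule, to be made before outcomes are compared by arm. No extra data should be needed, since factors used for allocation are known at randomisation. Neither accrual nor conduct changes.

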#### Sample size

Target accrual will be set at 456, 228 in each arm, derived based on an assumption of 5-year bPFS of 90–91% with 5-fraction SABR, and designed to establish with 80% power and an α of 0.05 that 2-fraction SABR results in a 5-year bPFS that is not lower than the standard 5-fraction regimen by more than 7%. The noninferiority margin was chosen to be approximately one half of the absolute difference in 5-year bPFS observed among contemporary superiority trials of dose escalation (15–16%) in similar risk patients. Under assumed failure rates and guarding against dropout, the final targeted accrual will be 502 patients.

#### Analysis plan

The primary endpoint of this study is failure from disease progression (FFDP), defined as clinical or biochemical disease recurrence (biochemical failure as per PSA nadir + 2 ng/mL), excluding death. Death with no evidence of progression will be treated as a competing risk in the survival models. This study will utilize both an intent-to-treat and per-protocol analysis of the primary and secondary endpoints, with time-to event duration originating at random assignment. Prognostic characteristics, treatment delivery, and toxicity will be reported using descriptive statistics. Time-to-event endpoints will be calculated using the Kaplan-Meier method [24] and compared using the log-rank test. HRs with 95% CI will be computed using the Cox proportional hazards regression model for the end point–specific hazard. Frequency distributions of grade (0 to 5) for selected adverse events will be compared using x^2^ tests. 2 × 2 sub-tables will be formed to evaluate the differences in risk of grade 2 or 3 events, and relative risk (RR) estimates with 95% CIs will be computed. The definitive analysis is planned to occur at 5 years, with two planned interim safety analysis at mean follow up of one and two years.

Secondary endpoints (unpowered) will include progression free survival (PFS), distant metastasis-free survival (DMFS), prostate cancer-specific survival (PCSS), longitudinal PSA response, and time to salvage treatment, also assessed at five years. Both patient-reported and physician-reported treatment related adverse effects at six months, one, and two years will be compared and reported. In the setting of multiple secondary endpoints, the Benjamini-Hochberg FDR correction procedure will be applied. Treatment related AE will be primarily objectively measured using the EPIC-26 evaluation. MIDs for each of the domains will be set as follows: 5 for bowel and hormonal, 6 for urinary obstructive, 11 for sexual, and 8 for urinary incontinence [25].

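### The trial is sized for an absolute 7-point non-inferiority margin at 5 years, but the only between-arm comparisons the Analysis plan states are a log-rank test of equality and a Cox HR, neither tied to that margin

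*Protocol article*

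**What the plan says.** The Objective and Study design sections of the protocol article describe a non-inferiority trial. The Sample size section fixes the hypothesis: the trial is "designed to establish with 80% power and an α of 0.05" that 5-year bPFS with 2 fractions is "not lower than the standard 5-fraction regimen by more than 7" percentage points. The control rate is an "assumption of 5-year bPFS of 90–91% with 5-fraction SABR". The margin is justified as about half of an absolute difference of 15–16% seen in dose-escalation trials, so it is on the absolute-difference scale. The result is: "Target accrual will be set at 456, 228 in each arm", raised to 502 for dropout.

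The Analysis plan is the only analysis text. On time-to-event endpoints it says: "Time-to-event endpoints will be calculated using the Kaplan-Meier method [24] and compared using the log-rank test". It continues: "HRs with 95% CI will be computed using the Cox proportional hazards regression model" for the endpoint-specific hazard. It plans intent-to-treat and per-protocol analyses, treats death without progression as a competing risk, and places the definitive analysis at 5 years. The 7-point margin does not appear there. Nor do an interval for the 5-year difference, a margin on the HR scale, or a rule for declaring non-inferiority.

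**The concern.** The log-rank null hypothesis is equal hazards. Rejecting it shows a difference; failing to reject it shows nothing about whether a deficit of 7 points has been excluded. A Cox HR with its interval could support non-inferiority, but only against an HR margin, and none is given.

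This is more than an omitted detail. The article names a method of comparison, and that method answers a different question from the one behind the sample size. An analyst who follows the text would have to choose the scale, the margin on that scale and the confidence level later, possibly after seeing data. Those choices change both the false-claim rate and the power of the trial's central conclusion.

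**Working it through.** **Inputs.** From Sample size: control 5-year rate 90–91%, margin 7 points, power 80%, α 0.05 (side not stated), 228 per arm. From Analysis plan: log-rank test; Cox HR with 95% CI. Assumed here, not stated in the article: equal true rates when power is computed, exponential event times, no dropout and, unless noted, everyone followed for exactly 5 years.

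**1. Reproduce 228 per arm.** Non-inferiority on a difference of two proportions, p in both arms:

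n = 2p(1 − p)(z₁₋α + z₀.₈)² / 0.07²

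- p = 0.90, one-sided 0.05: 0.18 × (1.645 + 0.842)² / 0.0049 = 227.1, rounded up to 228. Exact match.
- p = 0.91, one-sided 0.05: 207.
- p = 0.90, one-sided 0.025: 289.

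Of these, only the absolute difference at 90% and one-sided 0.05 gives 228.

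**2. Log-rank test when the truth lies on the margin.** HR = ln(p − 0.07)/ln(p); events d = 228 × [(1 − p) + (1 − p + 0.07)]; power = Φ(ln(HR) × √d/2 − 1.96).

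| True rates | HR | Events | Power | Non-significant | Non-significant, simulated (20,000 trials) |
|---|---|---|---|---|---|
| 90% vs 83% | 1.77 | 61.6 | 60.9% | 39.1% | 41.0% |
| 91% vs 84% | 1.85 | 57.0 | 64.0% | 36.0% | 37.8% |

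In the same simulations, the test of the 5-year difference against −7 points at one-sided 0.05 falsely declared non-inferiority in 5.1% and 5.2% of trials. If all 502 patients were followed (251 per arm), the log-rank test would still be non-significant in 34.9% and 31.8% by formula.

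**3. Non-inferiority on the HR scale, equal arms.** Events needed for 80% power at one-sided 0.05: 4 × (1.645 + 0.842)²/ln(HR)² = 76.1 at a margin of 1.77 and 65.5 at 1.85. Events expected by 5 years: 456 × 0.10 = 45.6 and 456 × 0.09 = 41.0.

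- One-sided 0.05: Φ(0.570 × √45.6/2 − 1.645) = 61.0%; Φ(0.614 × √41.0/2 − 1.645) = 62.7%.
- Stated 95% CI (1.96 in place of 1.645): 48.6% and 50.3%.

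Longer follow-up helps. Suppose uniform accrual over A years and analysis 5 years after the last entry. With hazard λ = −ln(p)/5, expected events are 456 × {1 − [e^(−5λ) − e^(−(5+A)λ)]/(λA)}. For A = 2 and A = 5 this gives about 54 and 66 events at 90%, and 49 and 60 at 91%. Power at one-sided 0.05 is then about 67 to 77%. The article gives no accrual period, so this range is illustrative.

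**4. Test of the 5-year difference, equal arms.** SE = √(2p(1 − p)/228) = 0.0281 at 90% and 0.0268 at 91%.

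| Level | 90% control | 91% control |
|---|---|---|
| One-sided 0.05 (90% CI) | Φ(2.491 − 1.645) = 80.1% | Φ(2.612 − 1.645) = 83.3% |
| One-sided 0.025 (95% CI) | Φ(2.491 − 1.96) = 70.2% | Φ(2.612 − 1.96) = 74.3% |

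**The case against.** The log-rank sentence is generic. It covers the primary endpoint together with PFS, metastasis-free survival, cancer-specific survival and time to salvage, and for the unpowered secondary endpoints log-rank and Cox are ordinary choices. The text never calls log-rank the confirmatory test. Kaplan-Meier estimation supplies 5-year rates, and Sample size supplies the margin to hold them against. This is a condensed article, and a statistical analysis plan that is not shown may contain the decision rule.

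Much of this stands, and it limits the point. A reader might infer that the trial will never test non-inferiority, or that the investigators intend to claim it from a non-significant log-rank test. The documents support neither. The 36 to 41% figure describes a misuse that the text leaves open, not a rule that it states. Nor are log-rank and an HR margin chosen afterwards the only routes, since comparing 5-year rates with 7 points is available and matches the design. An HR margin could also be derived from the stated rates, and power on that scale depends on follow-up, which continues annually after year 5 under Patient monitoring.

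What does not stand is that the gap is mere silence. The article does say how the arms will be compared, and that comparison does not match the hypothesis. The intended rule cannot simply be read off either: the only confidence level given is 95%, while the sample size rests on one-sided 0.05.

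**Conclusion.** The point holds in limited form: the sample size and the stated analysis address different hypotheses. Of the options examined, only the test of the 5-year difference at one-sided 0.05 delivers the planned power (80 to 83%). The same test with a 95% CI has 70 to 74%. An HR margin has 61 to 63% at one-sided 0.05 with follow-up cut at 5 years, and remains below 80% in the longer follow-up scenarios examined. A non-significant log-rank result carries no assurance about the margin.

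The figures rest on exponential times, complete follow-up of 228 per arm, equal true rates for power, and control rates of 90–91%. The mismatch itself rests on none of these. It is a finding about the published text and does not establish what an unseen analysis plan contains.

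**What to change.** In the Analysis plan, name the between-arm difference in 5-year FFDP as the primary analysis. Estimate it consistently with the stated handling of death as a competing risk, for example from cumulative incidence of progression. Declare non-inferiority only if the lower one-sided 95% limit (two-sided 90% CI) for 2-fraction minus 5-fraction lies above −7 points, and state in Sample size that α is one-sided 0.05, which is what reproduces 456.

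If the two-sided 95% CI is to be the decision interval, restate power for 228 per arm as about 70% (90% control) to 74% (91% control), or re-size: 80% power would need 289 or 263 per arm respectively.

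Report the result in both the intent-to-treat and per-protocol sets already planned. Keep the log-rank test and Cox HR as supportive analyses, and say that a non-significant log-rank test is not evidence of non-inferiority.

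With the 90% CI, the cost is wording only, with no extra patients or data. With the 95% CI, it is either a less favourable stated power or a larger trial.

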There exists, to date, limited data on the safety and effectiveness of prostate SABR delivered in fewer than five fractions. A recent proof-of-concept study by Greco et al. compared single-dose SABR of 24 Gy to 5 fractions of 9 Gy in favorable intermediate and unfavorable intermediate risk patients [14]. They utilized an air-filled rectal balloon to limit rectal motion and planned with no posterior planning target margin. The results demonstrated comparable four-year PSA outcomes for favorable intermediate disease though inferior PFS for unfavorable intermediate disease. Objective and patient reported GU and GI toxicities were not significantly different, though one of the 15 patients in the single-fraction arm experienced delayed grade 3 urethral stenosis. Magli et al. published acceptable 1-year toxicity outcomes for a novel three-fraction regimen of SABR for low- and favorable intermediate-risk patients, to a dose of 40 Gy. MRI-based planning was utilized, gold fiducials and a hydrogel spacer were placed, and a catheter was inserted in the bladder for each fraction [15]. They observed rates of 11.9% and 1.7% acute grade 2 and 3 urinary toxicity, respectively, and 8.5% acute grade 2 rectal toxicity, all of which resolved by 12 months. Alayed et al. published safety and efficacy results of their prospective single-cohort study of low- and intermediate-risk patients undergoing a two-fraction SABR regimen to a dose of 26 Gy [16]. Radiation was delivered to the prostate alone using a 3 mm uniform expansion. The study was performed prior to development and standardization of peri-rectal hydrogel spacers. On their sample of 30 patients, they reported no acute grade 3 + GI or GU toxicity, and one instance each in later follow up, comparable or even slightly better than that from five-fraction protocols. An additional phase-II study has begun accruing of five vs. two fractions of SABR for low- and intermediate-risk prostate cancer (ClinicalTrials.gov identifier: NCT04984343), though requiring MRI-based adaptive therapy technology and utilizing lower radiation doses.

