#### Endpoints

**Primary endpoint**.

Freedom from disease progression (FFDP), defined as clinical failure or biochemical failure per the Phoenix definition [20].

**Secondary endpoints**.

Progression free survival (PFS), defined as biochemical failure, clinical failure, or death from any cause.Distant metastasis free survival [21].Prostate cancer specific survival (PCSS).Longitudinal PSA response.Time to salvage treatment.Physician-reported GU/GI toxicity at 1, 3, 6, 9, 12, 18, 24-months (CTCAE).Patient-reported GU/GI toxicity at 1, 3, 6, 9, 12, 18, 24-months (IPSS, EPIC, SHIM).

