#### Patient monitoring

Baseline assessment will include PSA, quantitative urinary function (IPSS), sexual health (SHIM) score, and a global quality of life measure (EPIC-26). Follow up will occur at 1 month, 3 months, continuing at 3-month intervals through 1 year, then every 6 months from years 2–5, followed by annually thereafter. PSA will be recorded in follow up at 3, 6, 9, and 12 months in the first year, then every 6 months thereafter through five years, then annually. IPSS, SHIM and EPIC scores will be recorded during each follow up.

Adverse events (AE) will be described using the grading scales found in the revised NCI Common Terminology Criteria for Adverse Events (CTCAE), version 5.0. An AE is defined as any untoward medical occurrence associated with the use of a medical intervention, which in the context of this trial include radiopaque hydrogel spacer and fiducial marker placement, and radiation therapy. The following AEs should be assessed and recorded at each protocol mandated data collection interval: dysuria, hematuria, incontinence, urinary retention, diarrhea, rectal hemorrhage, fatigue. Full schedule of patient monitoring is summarized in Table 4.

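### Toxicity endpoints are set at seven times, but the one dated between-arm comparison covers three of them and leaves out both acute visits

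*Protocol article*

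**What the plan says.** **Endpoint definition** (Endpoints, secondary). The physician-reported endpoint is "Physician-reported GU/GI toxicity at 1, 3, 6, 9, 12, 18, 24-months (CTCAE"). The patient-reported endpoint has the same seven times: "Patient-reported GU/GI toxicity at 1, 3, 6, 9, 12, 18, 24-months (IPSS, EPIC, SHIM").

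**Comparison** (Analysis plan). "Both patient-reported and physician-reported treatment related adverse effects at six months, one, and two years will be compared and reported". This is the only sentence on comparing toxicity between arms that gives dates.

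**Undated analyses** (Analysis plan). Toxicity is to be described. Grade distributions from 0 to 5 for selected adverse events are to be compared by chi-square test. In addition, "2 × 2 sub-tables will be formed to evaluate the differences in risk of grade 2 or 3 events", with relative risks and 95% CIs. None of these has a time window.

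**Multiplicity** (Analysis plan). A Benjamini-Hochberg correction is to be applied across the secondary endpoints.

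**Data collected** (Patient monitoring, and Table 4). The visit schedule reads: "Follow up will occur at 1 month, 3 months, continuing at 3-month intervals through 1 year, then every 6 months from years 2–5, followed by" annual visits. At those visits, "IPSS, SHIM and EPIC scores will be recorded during each follow up". For physician-graded events, "The following AEs should be assessed and recorded at each protocol mandated data collection interval".

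**The concern.** The same secondary endpoints have one set of times where they are defined and a smaller set where they are analysed. An analyst who follows the Analysis plan sentence compares the arms at 6, 12 and 24 months and makes no comparison at 1 or 3 months.

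The protocol's own background shows why this matters. The 3-fraction study it cites had acute urinary toxicity of 11.9% (grade 2) and 1.7% (grade 3) and acute grade 2 rectal toxicity of 8.5%, all resolved by 12 months. If the dated comparison uses the grade present at the visit, such events are invisible at 12 and 24 months and may be gone by 6 months.

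Toxicity is not peripheral here. The Objective includes quality-of-life non-inferiority, and the Conclusion looks to a regimen that is non-inferior in safety as well as efficacy. With two sets of times on paper and undated tables beside them, the times to be tested could be settled after the data are seen.

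**Working it through.** The plan gives no computed figure on this point, so the check sets the stated times side by side.

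1. **Endpoint times** (Endpoints): {1, 3, 6, 9, 12, 18, 24} months, for both physician and patient report.
2. **Dated comparison times** (Analysis plan): {6, 12, 24} months.
3. **Difference:** {1, 3, 6, 9, 12, 18, 24} − {6, 12, 24} = {1, 3, 9, 18}. Coverage is 3/7 = 43%. The article gives no length for the acute period. Taking it as through month 3, both acute visits fall in the uncovered set.
4. **Scheduled visits to 5 years** (Patient monitoring, Table 4): 1, 3, 6, 9, 12, 18, 24, 30, 36, 42, 48, 54 and 60 months, which is 13. Every endpoint time is a scheduled visit, so the uncovered times are not explained by missing data. Six visits (30 to 60 months) come after the last endpoint time. Neither the endpoint list nor the dated comparison uses them, although the definitive analysis is planned at 5 years.
5. **Effect on the test family.** As an illustration, count one test per instrument (CTCAE, IPSS, EPIC, SHIM) and time. Three times give 4 × 3 = 12 tests; seven give 4 × 7 = 28. The Benjamini-Hochberg thresholds depend on that count, and the article does not say which applies.
6. **Grade cut-point.** The chi-square tables run over grades 0 to 5. The 2×2 tables name grades 2 and 3. A 2×2 table has only an event and a non-event column, so on a literal reading a man with a grade 4 or 5 event is either a non-event or left out. Cut-points at grade ≥2 and grade ≥3 avoid both.

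**The case against.** The strongest reply is that the Analysis plan does more than the dated sentence. It plans descriptive reporting, chi-square tests and relative risks with no time limit, and it commits to intention-to-treat and per-protocol analysis of the secondary endpoints, which include months 1 and 3. The three-time sentence may simply pick out the main reporting times. This stands to a point: the document does not show that acute data go unanalysed. But it also does not say that the undated tables cover the acute period, or whether they use worst grade, grade at a visit or cumulative events. They leave the conflict where it was.

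A second reply is that a journal article condenses a fuller plan. That is fair for details left unsaid, such as how events are counted. It does not cover two explicit and different lists of times for the same endpoints.

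Third, grade 4 and 5 events remain in the chi-square tables, and the monitoring committee reviews every grade 3 to 5 toxicity. So the 2×2 wording is a drafting fault rather than a loss of data.

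Fourth, toxicity is a secondary, unpowered endpoint. There are two interim safety analyses, annual committee reviews, and acute reviews after the first 3 and first 20 patients treated with 2 fractions. These limit the consequences, but they are safety monitoring and do not replace the final randomized comparison.

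**Conclusion.** The inconsistency is real and should be corrected. Four of seven endpoint times, including months 1 and 3, have no dated between-arm comparison, and the grade cut-point in the 2×2 tables is badly worded. Calling months 1 and 3 the acute visits rests on taking the acute period as through month 3. No sample size or power figure is affected.

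Three stronger readings are tempting, and the documents do not support them:

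- **That acute toxicity will not be compared at all.** The undated analyses could include it.
- **That the plan contradicts itself after 24 months.** The endpoint list and the dated comparison both stop at 24 months. The later data are an unused resource, and the full plan may use them.
- **That a particular number of late events would be missed.** In the cited 2-fraction cohort of 30 men, "they reported no acute grade 3 + GI or GU toxicity, and one instance each in later follow up". Scaling 1/30 to an arm of 502/2 = 251 gives 251/30 = 8.4 events of each type. But the exact 95% CI for 1/30 is about 0.1% to 17%, or roughly 0.2 to 43 events. That cohort received 26 Gy, before spacers were standard, and the article does not say when the events occurred. The cohort supports looking at late toxicity but gives no usable count.

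**What to change.** Revise the toxicity text of the Analysis plan as follows:

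1. Use the same times as the Endpoints section, and say which of them are compared between arms.
2. **Acute:** compare the worst CTCAE grade through month 3, for GU and GI separately.
3. **Late:** compare the cumulative incidence of first grade ≥2 and first grade ≥3 GU and GI toxicity after month 3, using the adverse event data already scheduled to 5 years, with death as a competing event. Report the risk difference with its CI.
4. Replace the grade 2 or 3 wording with grade ≥2 and grade ≥3, and give each table a time window.
5. State which of these comparisons enter the Benjamini-Hochberg family and which are descriptive.

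The cost is modest extra analysis and a somewhat larger test family. No new visits or data items are needed.
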